# Rationale and design of a multicenter randomized controlled study to evaluate the preventive effect of ipragliflozin on carotid atherosclerosis: the PROTECT study

**DOI:** 10.1186/s12933-016-0449-7

**Published:** 2016-09-13

**Keywords:** Atherosclerosis, Intima-media thickness (IMT), Ipragliflozin, SGLT2 inhibitor, Type 2 diabetes mellitus

## Abstract

**Background:**

Type 2 diabetes mellitus is associated strongly with an increased risk of micro- and macro-vascular complications, leading to impaired quality of life and shortened life expectancy. In addition to appropriate glycemic control, multi-factorial intervention for a wide range of risk factors, such as hypertension and dyslipidemia, is crucial for management of diabetes. A recent cardiovascular outcome trial in diabetes patients with higher cardiovascular risk demonstrated that a SGLT2 inhibitor markedly reduced mortality, but not macro-vascular events. However, to date there is no clinical evidence regarding the therapeutic effects of SGLT2 inhibitors on arteriosclerosis. The ongoing PROTECT trial was designed to assess whether the SGLT2 inhibitors, ipragliflozin, prevented progression of carotid intima-media thickness in Japanese patients with type 2 diabetes mellitus.

**Methods:**

A total of 480 participants with type 2 diabetes mellitus with a HbA1c between 6 and 10 % despite receiving diet/exercise therapy and/or standard anti-diabetic agents for at least 3 months, will be randomized systematically (1:1) into either ipragliflozin or control (continuation of conventional therapy) groups. After randomization, ipragliflozin (50–100 mg once daily) will be added on to the background therapy in participants assigned to the ipragliflozin group. The primary endpoint of the study is the change in mean intima-media thickness of the common carotid artery from baseline to 24 months. Images of carotid intima-media thickness will be analyzed at a central core laboratory in a blinded manner. The key secondary endpoints include the change from baseline in other parameters of carotid intima-media thickness, various metabolic parameters, and renal function. Other cardiovascular functional tests are also planned for several sub-studies.

**Discussion:**

The PROTECT study is the first to assess the preventive effect of ipragliflozin on progression of carotid atherosclerosis using carotid intima-media thickness as a surrogate marker. The study has potential to clarify the protective effects of ipragliflozin on atherosclerosis.

*Trial registration* Unique Trial Number, UMIN000018440 (https://upload.umin.ac.jp/cgi-open-bin/ctr_e/ctr_view.cgi?recptno=R000021348)

**Electronic supplementary material:**

The online version of this article (doi:10.1186/s12933-016-0449-7) contains supplementary material, which is available to authorized users.

## Background

Type 2 diabetes mellitus (T2DM) is characterized by prolonged systemic insulin resistance, resultant impaired insulin insufficiency, and life-threatening micro- and macro-vascular complications [1–4]. The risk of cardiovascular (CV) disease is already increased in the pre-diabetic state of impaired glucose tolerance (IGT) and is associated to a greater degree with impaired fasting and/or 2-h plasma glucose than with HbA1c levels [5–8]. Abnormal glycemic metabolism therefore has a central role in diabetic pathophysiology. However, whether glucose-lowering treatments reduce the risk of future CV events still remains controversial, despite the legacy-effect of long-term intensive glycemic intervention [9–11]. Given the multi-factorial nature of T2DM progression, early medical intervention using a comprehensive approach according to an individual’s medical background needs to be emphasized in the management of the disorders [12, 13]. However, relevant risk factors are often not controlled optimally, and no conventional anti-diabetic agents can easily achieve such therapeutic goals. Given the worldwide increase in the number of patients with the metabolic syndrome including obesity and diabetes [14, 15], early establishment of therapeutic strategies to prevent the subsequent occurrence of obesity/diabetes-related CV complications is urgently required.

Sodium glucose cotransporter 2 (SGLT2) inhibitors are novel glucose-lowering agents that increase urinary glucose excretion by modulating selective inhibition of SGLT2 in the proximal renal tubule [16]. SGLT2 inhibitors alleviate glucotoxicity in an insulin-independent manner and improve beta-cell dysfunction, and therefore may have indirect metabolic benefits [17]. Of the SGLT2 inhibitors, ipragliflozin was developed in Japan. There is evidence that ipragliflozin has the favorable metabolic effects, including improved glycemic control, and decreased blood pressure (BP), body weight (BW), and visceral adipose tissue, indicating a potential CV protective effect [18, 19]. Several mega-clinical trials designed to clarify the effects of SGLT2 inhibitors on clinical CV outcomes are now in progress [20]. Of these trials, EMPA-REG OUTCOME trial showed that empagliflozin markedly reduced the risk of CV mortality compared to placebo [21]. Although CV mortality and worsening of heart failure were both decreased dramatically, empagliflozin treatment failed to reduce macro-vascular events, such as non-fatal myocardial infarction and stroke. The clinical impact of SGLT2 inhibitors on CV benefits has therefore attracted considerable attention, although the mechanisms by which SGLT2 inhibitors exert these benefits beyond glucose-lowering are not fully understood. In particular, clinical evidence regarding the therapeutic effect of SGLT2 inhibitors on arteriosclerosis in patients with diabetes is still lacking. The effects on arteriosclerosis of other anti-diabetic agents, such as pioglitazone and dipeptidyl peptidase 4 (DPP-4) inhibitors, have been evaluated in randomized clinical trials using surrogate markers, such as carotid intima-media thickness (IMT) [22–25]. This method is well-established and has good reproducibility and reliability to reflect the clinical severity of systemic atherosclerosis, and is therefore useful for evaluating drug efficacy.

On the basis of this background, the PROTECT study was designed to evaluate the anti-atherosclerotic effect of ipragliflozin using IMT as a surrogate marker for the risk of CV events and also to clarify the mechanisms by which SGLT2 inhibitors may improve CV outcomes. This study may provide novel evidence regarding SGLT2 inhibitor-mediated pharmacological intervention on carotid atherosclerosis.

## Methods

### Study overview and design

The PROTECT study is an ongoing, multicenter, prospective, randomized, open-label, blinded-endpoint, parallel group, investigator-initiated clinical trial (phase IV). The study will test the hypothesis that compared to standard care alone, the addition of ipragliflozin to standard care in T2DM may suppress the progression of carotid atherosclerosis, accompanied by an improvement in glycemic and lipid metabolism and vascular function. After recruitment and randomization of the patients into groups with or without ipragliflozin, each treatment is continued for 24 months, and the long-term safety and effects of ipragliflozin on CV systems then evaluated.

The study protocol was approved by the local institutional review boards and independent ethics committees. The study will be conducted in full compliance with the articles of the Declaration of Helsinki and according to the Ethical Guidelines for Medical and Health Research Involving Human Subjects established by the Ministry of Health, Labour, and Welfare and Ministry of Education, Culture, Sports, Science, and Technology. The PROTECT study was registered by the UMIN in July 2015 (ID: 000018440).

### Study population and recruitment

We aim to recruit a total of 480 participants across approximately 35 sites in Japan. Recruitment for the study began in September 2015 and will end in December 2017. Eligible participants for the study are T2DM patients who comply with all the enrollment criteria. The detailed inclusion and exclusion criteria are listed in Table 1. Briefly, patients will be enrolled if they are aged ≥20 year, diagnosed as having T2DM in accordance with the Japanese guidelines [26], with a HbA1c between 6.0 and 10.0 % despite diet and exercise therapy and/or taking standard medications for at least 3 months prior to randomization. After initial screening using previous medical records, each participant is required to receive an adequate explanation of the study plan, with written informed consent then being obtained.

**Table 1 Tab1:** Detailed inclusion and exclusion criteria

Inclusion	Exclusion
Adults (aged ≥20 years)	Type 1 diabetes mellitus
T2DM with 6.0 % ≤ HbA1c < 10.0 % despite diet and exercise therapy and/or the standard medications for at least 3 months prior to randomization	History of severe ketosis, diabetic coma, or
The patient provided written informed consent to participate in the study	Precoma attack ≤6 months prior to informed consent
	Patients with severe infection or trauma at trial screening
	Patients in perioperative period around trial screening
	Severe renal dysfunction (eGFR **<** 45 ml/min/1.73 m^2^) or patients receiving dialysis
	History of coronary artery disease, coronary vascularization, open-heart surgery, stroke, or transient ischemic attack ≤3 months prior to eligibility
	CHF (NYHA functional classification III and IV)
	History of administration of SGLT2 inhibitor 1 month prior to study initiation
	Pregnant or suspected pregnancy in females
	Lactating female
	History of hypersensitivity to ingredients of ipragliflozin
	Considered inappropriate for the study by investigators due to other reasons, such as malignancy

*CHF* chronic heart failure, *eGFR* estimated glomerular filtration rate, *NYHA* New York Heart Association, *SGLT2* sodium glucose cotransporter 2, *T2DM* type 2 diabetes mellitus

### Study outline and follow up

After informed consent has been obtained and the eligibility assessment is completed, all eligible participants will be randomized and assigned into either the ipragliflozin group or standard-care (control) group. Follow-up visits are scheduled at 3, 6, 12 and 24 months (Fig. 1). All participants will see their usual-care physicians at each visit to receive usual-care and individualized appropriate treatment according to their background disease, in addition to administration of the study drug.

**Fig. 1 Fig1:**
[figure not shown]
Study outline

### Randomization and treatment

Eligible participants with appropriately signed informed consent will be randomized to either the ipragliflozin group or control group (ratio 1:1) using the web-based minimization method with biased coin assignment balancing [27, 28] for age (<65, ≥65 year), HbA1c level (<7.0, ≥7.0 %), systolic BP (<135, ≥135 mmHg), use of statins, and use of biguanides at the time of screening.

All participants will be followed-up for 24 months. Although a specific numerical goal in glycemic control such as HbA1c level is not set for the study, all participants need to be treated to achieve a personalized goal recommended by the treatment guideline in Japan (details in Additional file 1) [26]. Participants who are assigned to the ipragliflozin group receive ipragliflozin 50 mg once daily in addition to their background medical therapy. In accordance with official recommendation regarding use of SGLT2 inhibitor from the Japan Diabetes Society [29], patients aged ≥75 years should be most carefully followed up with particular attention to development of volume depletion-related adverse drug reactions [30]. If the personalized goal is not achieved, the dose of ipragliflozin can be increased by the investigators to 100 mg once daily. Participants who are assigned to the control group continue their background therapy. Within the appropriate range of the therapeutic goal, the participant’s background therapy will be, in principle and if possible, unchanged during the study in both groups. However, if participants cannot achieve their glycemic goal, co-administration of anti-diabetic agents other than SGLT2 inhibitors or increased dosages of the other anti-diabetic agents in both groups may be considered by investigators, with caution being taken to prevent the development of hypoglycemia. However, because pioglitazone is known to have a suppressive effect on the progression of IMT, compared to glimepiride [22], it is prohibited to prescribe it or change its dose during the study. After the study is completed, all participants can continue any anti-diabetic treatment in accordance with their individual condition.

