#### Measurement of carotid IMT

The protocol and method for measuring carotid IMT have been described in detail previously [25, 31, 32]. In brief, the carotid ultrasound examinations using standardized imaging protocols and systems equipped with >7.5 MHz linear transducers will be performed at each local site and then measured at a core laboratory (Tsukuba University) at baseline and 24 months after randomization. Expert trained sonographers who have attended a lecture on measuring carotid IMT will carry out the procedure according to the Mannheim carotid IMT consensus [33, 34]. The head position and probe angle of the ultrasound approach will be set using a ruler located just cephalad (Fig. 2). Longitudinal B-mode images, perpendicular to the ultrasound beam, with a 3–4 cm imaging depth, will be recorded in the distal common carotid arteries (CCA), carotid bulbs, and proximal internal carotid arteries (ICA) on both sides. The lateral probe incidence is used to obtain CCA images, using external landmarks and an original semicircular protractor developed for this purpose. The mean CCA-IMT indicates the average IMT value of the right and left CCA-IMT, 10 mm from the bulb. The following far wall IMTs will be measured; maximum IMT of the CCA and mean and maximum IMTs of the bulb and ICA. The optimized R-wave gated still frames of the carotid IMT will be stored as JPEG files, with all the parameters collected and measured at the core laboratory. An expert analyzer blinded to the allocation and clinical information of the subjects will measure all the IMT values using an automatic IMT measurement software program (Vascular Research Tools 5, Medical Imaging Applications, Iowa, USA) [35]. The software program identifies the lumen/intima and the media/adventitia borders in this region and calculates the distance between them.

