### Statistical considerations

#### Sample size estimation

Due to the lack of data on the effect of SGLT2 inhibitors on carotid IMT, we referred to the statistical data from the CHICAGO study [22] and PROLOGUE study [25]. In the CHICAGO study, pioglitazone caused a significant inhibition of the progression of CCA-IMT (−0.0010 mm after 72 weeks), compared to glimepiride (+0.0120 mm after 72 weeks). We estimated the changes from baseline would be −0.0013 mm (pioglitazone) and +0.016 mm (glimepiride) after 96 weeks. Based on the assumption that ipragliflozin may inhibit the progression of CCA-IMT to the same extent as pioglitazone, we estimated the group difference as 0.016 (ipragliflozin −0.001 and control +0.015) ±0.06 (standard deviation). At a significant level of 5 % (two-sided), the sample size of 222 patients per arm provides a power of 80 % for each comparison. Allowing for a dropout rate of 5 %, 240 patients in each arm (a total of 480 patients) provides sufficient statistical power for the study.

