#### Statistical analysis plan

The analyses of the primary and secondary endpoints will be performed in the full analysis set (FAS), which includes all participants who received at least one dose of treatment during the study period and did not have any serious violation of the study protocol such as not providing informed consent, registration outside of the study period, or data collected after commencement of treatment.

Summary statistics will be calculated for the baseline characteristics including the frequencies and proportions for categorical variables and means ± standard deviations for continuous variables. The patient characteristics will be compared using Chi square tests for categorical variables, t tests for normally distributed continuous variables, or the Wilcoxon rank sum tests for continuous variables with a skewed distribution.

The analysis plan is similar to that used in previous studies we have conducted [25, 31, 32]. In brief, for the primary analysis comparing treatment effects, the baseline-adjusted means and their 95 % confidence intervals, estimated by analysis of covariance of the change in average carotid IMT at 24 months, will be compared between the treatment groups (ipragliflozin group vs. control group). The results will be adjusted by allocation factors. The primary analysis will not include missing observations, with the mixed effects model for repeated measures (MMRM) being used as a sensitivity analysis to examine the effect of missing data. In addition, MMRM will be used as a sensitivity analysis to examine the outcomes at baseline and 24 months modelled as a function of time, treatment, and treatment-by-time interaction. The secondary analysis will be performed in the same manner as the primary analysis.

All comparisons are planned and all *P* values will be two sided. *P* values <0.05 will be considered statistically significant. All statistical analyses will be performed using SAS software version 9.4 (SAS Institute, Cary, NC, USA). The statistical analysis plan will be developed by the principal investigator and a biostatistician before completion of patient recruitment and database lock.

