## Discussion

The PROTECT study is an ongoing, multicenter, prospective, randomized, investigator-initiated clinical trial that has the aim of assessing the add-on effect of ipragliflozin using carotid IMT as a surrogate marker of CV risk. Cardiac and vascular functional tests will also be evaluated as secondary endpoints. Eligible patients with T2DM will be assigned to ipragliflozin or conventional standard care groups. The primary endpoint is the change in mean IMT of the CCA from baseline to 24 months of treatment. The study has the potential to provide novel clinical evidence on the anti-atherosclerotic effect of ipragliflozin.

Carotid IMT is used widely as a noninvasive measure of systemic atherosclerotic state and to predict subsequent CV events and mortality [38, 39]. A number of studies have demonstrated that increased IMT correlates strongly with the risk of future CV disease in a wide range of populations, especially T2DM patients [40–44]. Measuring carotid IMT is also recognized as a useful surrogate marker for evaluating the efficacy of therapeutic interventions on CV risk factors and atherosclerotic diseases [37, 45–47]. Although the current study is a multicenter open-label design, repeated IMT measurements are planned in a blinded manner. The analyses will be carried out at a core laboratory according to global recommendations in order to avoid bias and measurement error between institutions [48]. The same systematic procedures for analysis of carotid IMT were used in our previous and other ongoing studies [25, 31, 32]. The reliability and reproducibility of measurements of carotid IMT will be highly certified in the current study.

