This study has several limitations. First, the PROTECT study is not a double blind placebo-controlled trial, but rather an open label design. Unexpected bias towards the assessment of outcomes resulting from the physicians’ choice of treatment may occur. To avoid this possible bias, there are strict requirements that the participants’ background treatment will, in principle and if possible, remain unchanged during the study. In addition, carotid IMT, a key endpoint in the study, will be measured at a central laboratory, and all the data will be managed and statistically analyzed in a blinded fashion. Second, because the duration of the study is 24 months, it is possible the additional anti-diabetic agents administered when glycemic control becomes worse, especially in the control group, may influence outcomes. It is therefore important to take into account that pioglitazone and some other DPP-4 inhibitors may also prevent progression of carotid IMT in patients with T2DM [22–24]. Third, because the investigators who are participating in the PROTECT study are mainly cardiologists, there may be potential variety of treatment or judgement in the management of diabetes. Therefore, the Steering Committee recommends clinical practice will be performed according to the participants’ comprehensive conditions based on the treatment guideline in Japan [26]. Last, patient’s renal function, estimated glomerular filtration rate (eGFR), is not included as an allocation factor, although patients with severe renal dysfunction (eGFR < 45 ml/min/1.73 m^2^) or receiving dialysis are excluded. The patient’s kidney function is one of major determinants of urinary glucose excretion by SGLT2 inhibitor treatment. Previous studies reported that urinary glucose excretion in patients with lower levels of eGFR was actually decreased, and improvement of glycemic control was lower than patients without impairment of renal function [87, 88]. However, there were SGLT2 inhibitor-induced reductions in body weight and blood pressure independently of patient’s renal function [89]. Thus, we have speculated that anti-atherosclerotic effect may be, in part, caused by ipragliflozin independently of glycemic control and renal function at baseline.

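### Adding site as a random intercept to the primary ANCOVA would be a nearly free gain in precision: scans are acquired at about 35 sites, but site is not among the covariates the plan names

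*Protocol article*

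**What the plan says.** All of the following is in the protocol article.

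- **Study population and recruitment:** 480 participants at approximately 35 sites.
- **Measurement of carotid IMT:** the ultrasound examinations "will be performed at each local site and then measured at a core laboratory". Acquisition is standardized by a common imaging protocol, trained sonographers, a ruler and protractor for head and probe position, and R-wave gating. One blinded analyzer reads all images with automatic software.
- **Randomization and treatment:** minimization with a biased coin on age, HbA1c, systolic blood pressure, "use of statins, and use of biguanides at the time of screening". Site is not listed.
- **Statistical analysis plan:** the primary analysis is a baseline-adjusted ANCOVA of the 24-month change, and "The results will be adjusted by allocation factors". Secondary endpoints are analysed in the same manner.
- **Discussion:** core-laboratory analysis is used "in order to avoid bias and measurement error between institutions". The limitations note that, with mainly cardiologists taking part, "there may be potential variety of treatment or judgement in the management of diabetes". They name eGFR as a factor left out of the allocation and do not mention site.

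**The concern.** Central reading removes differences between readers. It cannot undo what is already in the stored image, such as a different machine, a change of sonographer or equipment during the two years, or uneven acquisition quality. Adjusting for baseline deals largely with a stable site offset in IMT level, but not with site-specific drift in the change. Local co-treatment is a second route. Investigators may add or increase other anti-diabetic agents, and the limitations accept that such additions may influence outcomes.

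Allocation ignores site, and there are about 480/35 = 14 participants per site, so the arms will be unequal within many sites by chance. Any site-level shift in IMT change then adds noise to the treatment comparison. Power is planned at 80 %, so there is little reserve. What is at stake is a modest amount of precision that the data could supply at almost no cost.

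**Working it through.** **Inputs from Sample size estimation.** "we estimated the group difference as 0.016" mm; SD of change 0.06 mm; two-sided 5 %; 222 per arm "provides a power of 80 % for each comparison"; dropout 5 %; 240 per arm.

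**Assumption.** The share ρ of the variance of IMT change that lies between sites is not given. The range tried is 0 to 0.20. The 0.06 mm is taken as the total SD.

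**Step 1: the plan's own figure.** n per arm = 2(1.960 + 0.842)² × 0.06²/0.016² = 220.7, so 221. The exact t version gives 222 (power 80.05 %). The stated figure reproduces. Allowing for 5 % dropout, 222/0.95 = 234, so 240 covers it.

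**Step 2: power of the analysis without site.** Completers: 240 × 0.95 = 228 per arm, 456 in all. SE of the difference = 2 × 0.06/√456 = 0.00562 mm. Then 0.016/0.00562 = 2.847, and power = Φ(2.847 − 1.960) = 81.3 %. Site variance is already inside the 0.06, so this does not depend on ρ. In simulation (35 unequal sites, allocation ignoring site, 4000 runs per setting) power without site stayed at 80.4 to 81.2 % for ρ from 0 to 0.20, and type I error at 4.6 to 5.6 %.

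**Step 3: gain from a random site intercept.** Take m = 456/35 ≈ 13 completers per site. With allocation ignoring site, the expected treatment information relative to the analysis without site is

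I = [(m − 1)/(1 − ρ) + 1/(1 − ρ + mρ)]/m,

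and the SE ratio is 1/√I. For example, at ρ = 0.10: (12/0.90 + 1/2.20)/13 = (13.333 + 0.455)/13 = 1.061, so the SE ratio is 0.971 and power = Φ(2.847/0.971 − 1.960) = 83.5 %.

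| ρ | I | SE ratio, formula | SE ratio, simulated | Power, formula |
|---|---|---|---|---|
| 0 | 1.000 | 1.000 | 1.00 | 81.3 % |
| 0.02 | 1.004 | 0.998 | about 1.00 | 81.4 % |
| 0.05 | 1.020 | 0.990 | 0.988 to 0.99 | 82.0 % |
| 0.10 | 1.061 | 0.971 | 0.965 to 0.974 | 83.5 % |
| 0.20 | 1.176 | 0.922 | 0.920 to 0.93 | 87.0 % |

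The simulated column spans two simulations, one by generalized least squares (4000 runs per value) and one fitting the site variance by REML (3000 runs per setting). A further REML simulation at ρ = 0 gave power of 81.2 and 81.3 % for the two analyses, with type I error about 5 %. I also reads as an equivalent gain in patients: about 2, 6 and 18 % at ρ = 0.05, 0.10 and 0.20.

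The simpler ratio √(1 − ρ), which is 0.975, 0.949 and 0.894 at those shares, assumes that the site effects are known. It overstates the gain with 13 completers per site.

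**Step 4: the form of the site term matters.** With 35 fixed site effects, simulated power without and with site was:

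| ρ | Without site | 35 fixed effects |
|---|---|---|
| 0 | 81.0 % | 77.6 % |
| 0.02 | 80.4 % | 78.4 % |
| 0.05 | 80.7 % | 80.2 % |
| 0.10 | 81.2 % | 82.4 % |
| 0.20 | 80.4 % | 86.0 % |

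Fixed effects lose power up to about ρ = 0.05. The random intercept does not.

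**The case against.** **The plan is internally consistent.** The ANCOVA adjusts for the factors used in the minimization, type I error holds and the sample size reproduces. All of this stands, and it is why the point is an improvement and not an error.

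**The article condenses.** It describes the analysis in brief, and a later analysis plan could add site. That is fair. Still, the article does name its adjustment set, and site is not in it.

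**The gain rests on an undocumented share.** This also stands. Below about 5 % the gain is negligible, and nothing in the article supports a share as high as 20 %.

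**Acquisition is well standardized.** It is, and this together with baseline adjustment should keep stable site differences small. Drift in change over 24 months is less well covered, though the article reports none.

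A reader might draw three stronger conclusions that the document does not support.

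- *The comparison is biased or the test invalid.* It is not. Allocation ignores site, so imbalance within sites is chance, and its variance is counted in the residual.
- *The trial is too small.* If 0.06 were only the within-site SD, the total SD would be 0.0616 at ρ = 0.05 and 0.0632 at ρ = 0.10, with power of 79.3 and 77.1 %. But the article gives 0.06 as the SD of the change without any such split.
- *Site effects rival the 0.016 mm target.* At ρ = 0.05, 0.10 and 0.20 the site SD of change, 0.06√ρ, is 0.013, 0.019 and 0.027 mm. That is not the error in the treatment difference, because site effects average over sites and across both arms. Their part of the standard error is about √ρ × 0.00562 = 0.0013, 0.0018 and 0.0025 mm, already inside the total.

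The Discussion sentence on the core laboratory states a purpose. Narrowing it to reader differences would be editorial and is not part of this point.

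**Conclusion.** The point holds as a free improvement in precision. Scans come from about 35 sites, the named covariates are baseline IMT and the five allocation factors, and between-site variation in 24-month change therefore stays in the residual. A random site intercept would lower the standard error by about 1, 3 to 4 and 8 % at assumed shares of 5, 10 and 20 %, and raise power from about 81 % to about 82, 83 and 87 %. At 0 to 2 % it changes practically nothing.

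These figures assume a total SD of 0.06 mm, 456 completers, 35 sites and allocation that ignores site. They compare against a plain difference in means, so they show the contribution of site alone and not the full planned ANCOVA. The validity of the planned test and the stated sample size are not in question.

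**What to change.** In the Statistical analysis plan section, or in the analysis plan due before completion of recruitment and database lock, state that the primary ANCOVA includes site as a random intercept, with baseline IMT and the five allocation factors kept. Do the same for the secondary IMT analyses. Do not use 35 fixed site effects. With a random intercept, sites with very few participants need no pooling.

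The cost is one sentence, with no new data and no change to enrolment or randomization. The only downside is one extra variance component, which may be estimated as zero; the model then reduces to the planned ANCOVA. Fixing this in advance also removes a later choice between models with and without site.
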